#### Secondary outcome measures: self-assessment questionnaires

In addition to the neuropsychological tests, all participants will also complete paper-pencil versions of self-assessment questionnaires. The results from these questionnaires will mainly be used to adjust for the effects of possible confounders when analysing neuropsychological test data. The following self-assessment questionnaires will be used: Hospital Anxiety and Depression Scale (Zigmond and Snaith, 1983), Insomnia Severity Index (Bastien, Vallieres, & Morin, 2001), Cognitive Failure Questionnaire (Broadbent, Cooper, FitzGerald, & Parkes, 1982), Perceived Stress Scale (Levenstein et al., 1993) and Multidimensional Fatigue Inventory (Smets, Garssen, Bonke, & De Haes, 1995). Participants will also answer background questions regarding age, education, gender identity, occupation, time since injury/diagnosis, diagnosis, number of hours slept last night and medication, including medication during the last 24 hours.

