### Data collection and management

#### Assessment procedure

After reading and signing informed consent forms, patients will be randomised into one of two test sequences – either beginning with performing the Mindmore Remote tests at home, followed by traditional neuropsychological testing on-site at the clinic, or vice versa (figure 1). Mindmore Remote testing will be performed by the participants in their homes after being contacted by the psychologist by phone. The remote session will not be directly observed by the psychologist. In cases where the data collection is part of a larger neuropsychological examination, the validation battery will be performed first during that examination to avoid the effects of fatigue. The test will be administered in the order outlined in table 1. Healthy controls will be randomised in a similar manner as patients, and except that data collection might be a part of a larger neuropsychological examination for patients, the data collection will not differ between groups.

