**Figure 1 F1:**
[figure not shown]
Flow chart of the study. Note: After signing informed consent (1), participants will be randomised (2) into performing traditional neuropsychological examination (NPS) at the clinic first and then Mindmore Remote at home or vice versa (3).

All data collection will be performed by psychologists trained specifically for the task of neuropsychological examinations. The two test sessions will be performed within 2 weeks, with at least 1 day of resting in between. Each test session will last about 30–45 min, adding up to 1–1.5 hours of testing time for both assessments in total. As part of the traditional neuropsychological examination, patients will complete self-assessment questionnaires. After data collection, a subsample of 10 patients will be contacted and offered to participate in a semi-structured telephone interview regarding research question 3, covering themes of usability and the difference of undergoing neuropsychological assessment on a computer at home versus at the clinic with a psychologist.

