### Data analysis plan

Validation of Mindmore test against traditional paper-pencil neuropsychological test will be performed using Pearson and/or Spearman correlation coefficients depending on the distribution of data. To evaluate bias between methods, the Bland-Altman method^25^ will be used. In addition, multiple linear regressions will be performed to investigate and adjust for the influence of background variables, such as age, education, gender, diagnosis and time since injury/diagnosis. To establish neuropsychological profiles of diagnostic groups, descriptive data from each test will be presented, and analysis of variance, with and without covariates, will be performed to determine differences between groups. Due to multiple statistical analyses, adjustments for multiple comparisons will be considered.

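### The Cognitive Failure Questionnaire is assigned to confounder adjustment, although it reports on the same domain as the tests and is plausibly a consequence of the diagnosis

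*Protocol article*

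**What the plan says.** The section on self-assessment questionnaires in the protocol article is headed as secondary outcome measures, but it gives the instruments another main role: "The results from these questionnaires will mainly be used to adjust for the effects of possible confounders when analysing neuropsychological test data". The "Cognitive Failure Questionnaire" is one of the five instruments listed, alongside scales for anxiety and depression, insomnia, stress and fatigue. No exception is made for it.

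The Data analysis plan says that the regressions will adjust for "background variables, such as age, education, gender, diagnosis and time since injury/diagnosis". For the neuropsychological profiles it says that "analysis of variance, with and without covariates, will be performed to determine differences between groups". It does not name the covariates of that analysis. The validation analyses proper (Pearson or Spearman correlation, and Bland-Altman) are described without adjustment.

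Research question 2 under Objectives concerns profiles for Parkinson's disease and multiple sclerosis, and the Sample size section is argued from differences between groups.

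**The concern.** A confounder of a comparison between diagnoses, or between patients and controls, should be something that affects test performance without being produced by the diagnosis. Age and education fit that description. A self-report of cognitive failures does not fit it well. The Introduction says that cognitive and executive deficits are among the commonest symptoms in these patients, so on the protocol's own account diagnosis leads to deficit. A person with a deficit can be expected to report more failures, which makes the CFQ a proxy for the quantity under comparison.

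Holding the CFQ constant then compares patients and controls who report the same level of cognitive trouble. Part of the true contrast is removed, and the result carries the label of confounder adjustment. If the adjusted and unadjusted results differ, a reader would normally trust the adjusted one, although on this covariate it would be the distorted one. What is at stake is the profile question, not the validity question.

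**Working it through.** **The plan's own figures first.** The Sample size section gives 16 participants for a difference of one SD at 80% power and, with 50 per group, power of 0.999 for 1 SD and 0.706 for 0.5 SD. I read these as comparisons of two equal groups with two-sided alpha of 0.05 (the article does not state sidedness). The normal approximation gives n = 16 and power of 0.9988 and 0.705. The two-sample t-test gives n = 16.7 and power of 0.9986 and 0.697. The figures reproduce, and none is disputed here.

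**Inputs for the check.** The 50 per group and alpha of 0.05 come from the article. Three quantities are not in the documents and are assumed, all in within-group SD units and with both scales oriented so that higher means worse:
- d, the true group difference on the test;
- d_CFQ, the group difference on the CFQ;
- r, the within-group correlation between CFQ and test.

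**Formulas** (one covariate, common slope, equal groups):
- adjusted difference = d − r × d_CFQ
- share removed = r × d_CFQ / d
- SE of the adjusted difference = √(1 − r²) × √(2/50) × √(1 + d_CFQ²/4)
- power = Φ(adjusted difference / SE − 1.96)

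**A difference of 0.8 SD:**

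| r | d_CFQ | Adjusted difference | Share removed |
|---|---|---|---|
| 0.1 | 0.3 | 0.8 − 0.03 = 0.77 | 4% |
| 0.2 | 0.8 | 0.8 − 0.16 = 0.64 | 20% |
| 0.3 | 0.8 | 0.8 − 0.24 = 0.56 | 30% |
| 0.4 | 0.8 | 0.8 − 0.32 = 0.48 | 40% |

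**The two differences used in the Sample size section:**

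| d | r | d_CFQ | Adjusted difference | Share removed | Power at 50 per group |
|---|---|---|---|---|---|
| 0.5 | none | none | 0.50 | 0% | 0.705 |
| 0.5 | 0.1 | 0.3 | 0.47 | 6% | 0.65 |
| 0.5 | 0.3 | 0.5 | 0.35 | 30% | 0.43 |
| 0.5 | 0.5 | 0.8 | 0.10 | 80% | 0.08 |
| 1.0 | none | none | 1.00 | 0% | 0.999 |
| 1.0 | 0.1 | 0.3 | 0.97 | 3% | 0.998 |
| 1.0 | 0.5 | 0.8 | 0.60 | 40% | 0.90 |

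For the third row: SE = √0.91 × 0.2 × √1.0625 = 0.197; 0.35/0.197 = 1.78; 1.78 − 1.96 = −0.18; Φ(−0.18) = 0.43.

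The loss is proportionally larger for a moderate difference, where the stated power of 0.706 leaves little margin. If r or d_CFQ is close to zero, almost nothing is removed.

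**The case against.** The best reply is that no model containing the CFQ is written down. The questionnaire section says mainly, and speaks of possible confounders. The covariates named in the Data analysis plan include no questionnaire. The exact covariate set for each model is ordinary content for a statistical analysis plan. The group analysis is also run without covariates, descriptive data are shown for each test, and the heading already gives the CFQ the status of an outcome.

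Most of this stands, and it limits the harm, but it does not remove the point. The list of covariates is introduced as examples, so it excludes nothing. The one sentence that does assign the questionnaires a role assigns the CFQ to adjustment. That is something the article states, not a detail it leaves out.

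Three stronger readings are tempting, and the documents do not support them.

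- *Sleep and recent medication are recorded only at the clinic visit, so state at the remote session is unknown.* A reader might infer this from "As part of the traditional neuropsychological examination, patients will complete self-assessment questionnaires". But the items on "number of hours slept last night and medication, including medication during the last 24 hours" are listed separately as background questions, and no session is given for them. They may be asked at either session or at both. A condensed article may leave that to the full protocol.
- *Stable traits cannot matter, because each person takes both batteries.* This fails for the primary analysis, which is a correlation between persons. A trait that drives both scores, such as age, affects that correlation. A trait may also change the difference between methods: the ethics section notes that distress is easier to notice and counter in traditional testing.
- *The loss is 20–40%.* That range holds d_CFQ at 0.8 SD and varies only r. With a smaller CFQ shift and a weaker correlation, the loss is about 4%.

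**Conclusion.** The concern holds in a limited form. The article places a self-report of cognitive failures among the variables meant for confounder adjustment, without exception. If it enters the covariate-adjusted group comparisons, it can shrink real diagnostic differences. For a true 0.8 SD difference, the adjusted value would be about 0.77 to 0.48 SD across the assumed inputs. The documents cannot narrow that range. Calling the loss bias rests on the CFQ lying downstream of diagnosis, which the Introduction makes plausible but the study does not test.

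The unadjusted analysis of variance, the primary correlations and the Bland-Altman analysis stand as described. This is a flaw in one adjusted analysis that serves research question 2, and it does not threaten the primary aim.

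**What to change.** In the questionnaire section and the Data analysis plan, exclude the CFQ from the confounder set and report it by group as a secondary outcome, in line with the heading under which it is listed. If a CFQ-adjusted group model is still wanted, show it beside the unadjusted result and describe it as the difference at equal self-reported cognitive failures, not as a confounder-adjusted estimate.

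The cost is a change of wording. The CFQ is collected anyway, so no new data, visits or participants are needed.

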### Data collection and management

#### Assessment procedure

After reading and signing informed consent forms, patients will be randomised into one of two test sequences – either beginning with performing the Mindmore Remote tests at home, followed by traditional neuropsychological testing on-site at the clinic, or vice versa (figure 1). Mindmore Remote testing will be performed by the participants in their homes after being contacted by the psychologist by phone. The remote session will not be directly observed by the psychologist. In cases where the data collection is part of a larger neuropsychological examination, the validation battery will be performed first during that examination to avoid the effects of fatigue. The test will be administered in the order outlined in table 1. Healthy controls will be randomised in a similar manner as patients, and except that data collection might be a part of a larger neuropsychological examination for patients, the data collection will not differ between groups.

**Figure 1 F1:**
[figure not shown]
Flow chart of the study. Note: After signing informed consent (1), participants will be randomised (2) into performing traditional neuropsychological examination (NPS) at the clinic first and then Mindmore Remote at home or vice versa (3).

All data collection will be performed by psychologists trained specifically for the task of neuropsychological examinations. The two test sessions will be performed within 2 weeks, with at least 1 day of resting in between. Each test session will last about 30–45 min, adding up to 1–1.5 hours of testing time for both assessments in total. As part of the traditional neuropsychological examination, patients will complete self-assessment questionnaires. After data collection, a subsample of 10 patients will be contacted and offered to participate in a semi-structured telephone interview regarding research question 3, covering themes of usability and the difference of undergoing neuropsychological assessment on a computer at home versus at the clinic with a psychologist.

#### Sample size

To be able to show that one patient group has a different cognitive profile compared with other patients or healthy controls, the aim is to include 50 participants in each group, which is the recommendation for sample size in normative studies of neuropsychological tests.^24^ With alpha = 0.05 and a power of 80%, 16 participants would be enough to detect differences of one SD from the mean. With the goal of 50 participants in each group, this means a statistical power of 0.999 to detect differences of one SD from the mean, and a statistical power of 0.706 to detect differences of 0.5 SD from the mean.

### Data analysis plan

Validation of Mindmore test against traditional paper-pencil neuropsychological test will be performed using Pearson and/or Spearman correlation coefficients depending on the distribution of data. To evaluate bias between methods, the Bland-Altman method^25^ will be used. In addition, multiple linear regressions will be performed to investigate and adjust for the influence of background variables, such as age, education, gender, diagnosis and time since injury/diagnosis. To establish neuropsychological profiles of diagnostic groups, descriptive data from each test will be presented, and analysis of variance, with and without covariates, will be performed to determine differences between groups. Due to multiple statistical analyses, adjustments for multiple comparisons will be considered.

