**Methods and analysis:**

This study protocol describes a cross-sectional study aimed at validating the newly developed digitalized neuropsychological test battery Mindmore Remote in patients with neurological disorders and injuries. Diagnoses comprise traumatic brain injury, stroke, Parkinson’s disease, multiple sclerosis, brain tumour and epilepsy. 50 patients in each patient group will be included. In addition, 50 healthy controls will be recruited. All participants will undergo both testing with Mindmore Remote at home and traditional neuropsychological assessment face-to-face in a randomised order. The primary outcome is the association between tests from the Mindmore Remote battery and their equivalent traditional neuropsychological tests. Further, bias between methods and differences between groups will also be investigated.

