FAS	In FAS, a test of verbal production and executive functions, the participant is instructed to say as many words as possible during 1 min, starting with a specific letter. The test is performed in three trials using letters F, A and S, respectively.	Number of words produced over all trials.	Verbal Fluency from D-KEFS^14^

All tests will be performed using Swedish versions.

D-KEFS, Delis-Kaplan Executive Functions System; WAIS, Wechsler Adult Intelligence Scale; WMS, Wechsler Memory Scale.

Raw scores of the tests will be used as the main variables in the analyses. However, scaled scores (ie, those computed from the normative samples in the test manuals of the traditional tests and from the built-in norms in Mindmore Remote) might also be considered in some analyses.

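### Test order is randomised but enters none of the stated analyses; if both tests improve at the second session, the primary correlations can be attenuated and the limits of agreement widened

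*Protocol article*

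**What the plan says.** Under Assessment procedure, "patients will be randomised into one of two test sequences": remote testing at home and then clinic testing, or the reverse. For the control group, "Healthy controls will be randomised in a similar manner as patients". The text after Figure 1 sets the interval: "The two test sessions will be performed within 2 weeks, with at least 1 day of resting in between". No allocation ratio or stratification is stated.

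The abstract defines the main target: "The primary outcome is the association between tests from the Mindmore Remote battery and their equivalent traditional neuropsychological tests". Under the primary outcome measures, "Raw scores of the tests will be used as the main variables in the analyses".

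The Data analysis plan section has three steps that bear on this point. Validation against the traditional tests "will be performed using Pearson and/or Spearman correlation coefficients depending on the distribution of data". The agreement step begins "To evaluate bias between methods, the Bland-Altman method". In addition, multiple linear regressions are planned "to investigate and adjust for the influence of background variables, such as age, education, gender, diagnosis and time since injury/diagnosis". Order, sequence, period and practice are not mentioned in any of them.

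**The concern.** Table 1 pairs each remote test with a traditional test of a similar function, and each person takes both within days. If people do better at the second session, the gain falls on the traditional score in one half of participants and on the remote score in the other half. Averaged over a balanced sample, equal gains cancel in the mean difference. Their contribution to the variances and the covariance does not cancel. The two sequence groups are displaced in opposite directions, which adds variance to each score, adds a negative term to the covariance, and adds variance to the within-person differences.

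The correlation is the primary outcome, and the limits of agreement bear on the first research question, which asks about equivalence. An error from ignored order is systematic, so a larger sample does not reduce it. If order is split unevenly within a diagnosis, that group's mean bias shifts too.

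**Working it through.** **The plan's own figures.** The only computed figures are those under Sample size, for group differences. With two-sided alpha 0.05 and the normal approximation:
- n per group for 1 SD = 2 × (1.96 + 0.84)² = 15.7, so 16.
- Power with 50 per group for 1 SD = Φ(√25 − 1.96) = Φ(3.04) = 0.999.
- Power for 0.5 SD = Φ(2.5 − 1.96) = Φ(0.54) = 0.705, against 0.706 stated.

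These reproduce and do not depend on test order. The article gives no figure for the correlation or for the limits of agreement.

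**Assumptions.** Scores are scaled to unit SD within sequence and order is split 1:1. ρ is the correlation free of order effects. pR and pT are the second-session gains, in SD, on the remote and traditional tests. The documents give none of ρ, pR or pT, so ranges are shown.

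**Formulas.**
- Pooled r = (ρ − pR·pT/4) / √[(1 + pR²/4)(1 + pT²/4)]. With equal gains d this is (ρ − d²/4)/(1 + d²/4).
- Pooled SD of differences = √[2(1 − ρ) + ((pR + pT)/2)²]. With equal gains this is √[2(1 − ρ) + d²].
- The limits of agreement are ±1.96 times that SD.

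**Example, ρ = 0.70 and d = 0.3.** r = (0.70 − 0.0225)/(1.0225) = 0.663. The SD ratio is √(0.69/0.60) = 1.072.

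| ρ | d | r with order ignored | Limits without gain | Limits with order ignored | Widening |
|---|---|---|---|---|---|
| 0.70 | 0.1 | 0.696 | ±1.52 | ±1.53 | 0.8% |
| 0.70 | 0.2 | 0.683 | ±1.52 | ±1.57 | 3.3% |
| 0.70 | 0.3 | 0.663 | ±1.52 | ±1.63 | 7% |
| 0.70 | 0.5 | 0.600 | ±1.52 | ±1.81 | 19% |
| 0.80 | 0.5 | 0.694 | ±1.24 | ±1.58 | 27% |

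Over ρ from 0.5 to 0.8 and d from 0.1 to 0.5, r falls by about 0.004 to 0.11 and the limits widen by 0.5% to 27%. A simulation of 1,000,000 pairs at ρ = 0.70 agreed for d = 0.3 and 0.5. Removing the sequence-specific means brought r back to 0.70 and the limits to ±1.52. Spearman does not protect: 0.683 falls to 0.644 at d = 0.3 and to 0.579 at d = 0.5.

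**Other patterns at ρ = 0.70.**
- Only one test gains 0.3 SD: r = 0.692, limits 1.9% wider.
- Shifts of −0.3 and +0.3 SD: r = 0.707, limits unchanged.

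**Uneven order within a diagnosis.** With equal gains, the mean difference shifts by d × (32 − 18)/50 = 0.28d for an 18:32 split. That is 0.08 SD at d = 0.3 and 0.14 SD at d = 0.5. Under simple 1:1 randomisation (an assumption), a split at least this uneven has probability 0.065 per group of 50, and 1 − 0.935⁷, about 0.37, in at least one of the seven groups.

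**The case against.** The analysis section is one paragraph of a journal article. The covariate list is open, and a sequence term may stand in a fuller plan that is not shown. A reader might infer that the investigators decided to exclude order, and the text does not support that. What remains is that the article itself fixes the estimators. Its list is open only to further background variables, and a sequence covariate added there would still leave the correlation and Bland-Altman steps unadjusted.

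A reader might also infer that practice effects will lower the correlations. The documents do not support that either. They report no practice effect, and several pairs are different instruments (mouse-click coding against WAIS-IV Coding, RAVLT against the WMS-III word list), so equal gains of 0.3 to 0.5 SD are not established. Up to 0.2 SD, r falls by at most about 0.02 and the limits widen by at most 5%.

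The shift is also small beside sampling error in one diagnosis: the 95% interval around r = 0.70 is 0.52 to 0.82 at n = 50. That stands for single groups. If all 300 patients are pooled, the interval is 0.64 to 0.75. A 0.3 SD gain then takes 0.037 of the 0.063 lower margin, and a 0.5 SD gain falls outside it. Likewise, the 0.08 SD bias shift lies below the standard error of a mean difference at n = 50 (0.775/√50 = 0.11 SD).

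Finally, no threshold for r or for the limits is stated, so no stated decision is reversed. With same-direction gains the error is conservative, because it understates validity.

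**Conclusion.** The point holds in conditional form. Order is randomised, and no analysis stated in the article uses it. If second-session gains have the same sign on both tests, ignoring order can attenuate the primary correlations and widen the limits of agreement even with perfectly balanced allocation. The size runs from negligible (gains up to 0.2 SD) to material (r 0.70 to 0.60 and limits 19% wider at 0.5 SD). It rests on assumed values of the correlation and the gain, and on equal gains. The effect is smaller if only one test gains, and r can rise slightly if the shifts are opposite. The sample size is not affected. A reading that the validity results would be invalid, or that the flaw is critical, goes further than the documents allow. This is a should-fix: only an analysis by sequence shows which case applies.

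**What to change.** Amend the Data analysis plan wording as follows.

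1. Report a sequence-adjusted correlation (partial, or pooled within sequence) alongside or in place of the unadjusted one.
2. For Bland-Altman, regress the within-person difference on sequence. Take the bias as the mean of the two sequence-specific means, and build the limits from the residual SD.
3. Add sequence to the regressions and report its effect, preferably for each test separately. Averaging the two sequence means corrects for an uneven split. It does not remove (pR − pT)/2 when the gains differ, and the test-specific sequence effects show whether that matters.

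Days between sessions could be added as an option; the article does not say that session dates are recorded. The cost is wording and about one degree of freedom per model. No extra participants or visits are needed.

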### Objectives

The primary aim of this project is to assess the convergent validity of Mindmore Remote tests by comparing them with standardised neuropsychological tests. We pose the following research questions:

Are the tests in Mindmore Remote equivalent to traditional neuropsychological tests in patients with traumatic brain injury, stroke, multiple sclerosis, Parkinson’s disease, epilepsy and brain tumour?Can the results from Mindmore Remote be transferred into neuropsychological profiles (eg, the distribution of performance across several tests) that can be used for patients with Parkinson’s disease and Multiple Sclerosis?How do the patients experience undergoing a neuropsychological evaluation on their own compared with traditional neuropsychological assessment in a physical meeting with a psychologist?

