### Participants

Patients with diagnoses of traumatic brain injury, stroke, Parkinson’s disease, multiple sclerosis, epilepsy and glioma who are referred for neuropsychological assessment at NHHC will be offered to participate in the study. The aim is to include 50 patients in each diagnostic group.

Healthy adults (*n*=50) will be recruited as controls through advertising at Umeå University Hospital. Since the patient groups will differ in age variance, the aim is to recruit a control group with a variance in age. The controls will be reimbursed for their participation (100 SEK; approximately €10).

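### Profile comparisons give unadjusted raw-score ANOVAs the same standing as adjusted ones, and no analysis of the pattern across tests is described

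*Protocol article*

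**What the plan says.** Research question 2 (Objectives) asks whether Mindmore Remote results can be turned into "neuropsychological profiles (eg, the distribution of performance across several tests" for use in Parkinson's disease and multiple sclerosis. The Sample size section justifies 50 per group by the wish to show that one patient group's cognitive profile differs from that of other patients or controls.

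Four statements fix how this is analysed:

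- **Description.** "To establish neuropsychological profiles of diagnostic groups, descriptive data from each test will be presented" (Data analysis plan).
- **Inference.** The same sentence continues: "analysis of variance, with and without covariates, will be performed to determine differences between groups". Neither version is given priority, and the ANOVA covariates are not listed. Age, education and gender are named in the preceding sentence, for the multiple linear regressions.
- **Scale.** "Raw scores of the tests will be used as the main variables in the analyses" (text below Table 1). Norm-based scaled scores "might also be considered in some analyses".
- **Controls.** "Since the patient groups will differ in age variance, the aim is to recruit a control group with a variance in age" (Participants). No age targets by diagnosis are stated.

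**The concern.** There are two separate problems.

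**Which comparison counts.** Raw neuropsychological scores are not age-normed. If two groups differ in age, an unadjusted raw-score comparison mixes the effect of diagnosis with the effect of age. It can create a difference or hide one, depending on which group is older. Running the ANOVA both ways without saying which one carries the conclusion gives the confounded test equal weight. It also leaves the choice open until both results are known.

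**Level or pattern.** A profile across tests is a statement about relative performance: this group is weaker on speed than on memory, say. Comparing groups on each test in its own units shows level only. A group uniformly lower on everything differs on every test and still has a flat profile. Table 1 mixes counts, where higher is better (symbol coding, word list, Corsi, FAS), with completion times, where higher is worse (Trail Making, Stroop). Means in these units cannot be read against each other.

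At stake is the answer to research question 2 and to the aim that sets the group size.

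**Working it through.** **1. The plan's own figures.** Two-group comparison, two-sided alpha 0.05, SD = 1, normal approximation:

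- n per group for 1 SD at 80% power: 2 × (1.96 + 0.84)² / 1² = 15.7, so 16. The plan says 16.
- Power at 50 per group for 1 SD: 1/√(2/50) = 5; Φ(5 − 1.96) = 0.9988. The plan says 0.999.
- Power at 50 per group for 0.5 SD: 0.5/√(2/50) = 2.5; Φ(2.5 − 1.96) = 0.705. The plan says 0.706.

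The figures reproduce. Each is the power for one mean difference on one test. None concerns age adjustment or a pattern across tests.

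**2. Unadjusted comparison with no true group effect.** The inputs are the within-group correlation r of age with score and the age gap g between two groups in within-group SDs of age. The document gives neither, so both are assumptions. The spurious standardised difference is d = r × g. With 50 per group the noncentrality is d × √(50/2) = 5d, referred to t on 98 degrees of freedom.

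| Assumed r | Age gap (SD) | Spurious d | Rejection rate (nominal 5%) |
|---|---|---|---|
| 0.3 | 0.5 | 0.15 | 11.5% |
| 0.3 | 1.0 | 0.30 | 31.8% |
| 0.3 | 1.5 | 0.45 | 60.6% |
| 0.5 | 0.5 | 0.25 | 23.6% |
| 0.5 | 1.0 | 0.50 | 69.7% |
| 0.5 | 1.5 | 0.75 | 96.0% |

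These rates are for one pairwise contrast on one test. With g = 0 the rate is 5%.

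**3. Adjusted comparison.** A linear age term removes this bias if the age effect is linear and parallel across groups. The standard error of the group difference is √[(1 − r²)(2/n + g²/(2(n − 1)))]. With n = 50 and r = 0.3, for a true difference of 0.5 SD:

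- g = 0: √(0.91 × 0.0400) = 0.191, power 0.737
- g = 1: √(0.91 × 0.0502) = 0.214, power 0.639
- g = 2: √(0.91 × 0.0808) = 0.271, power 0.447

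Adjustment therefore works, at a price in precision where group ages overlap little.

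**4. Pattern across tests.** The article does not give the structure of the ANOVA. Suppose it is run test by test, and a group has the same true 0.5 SD deficit on two tests, so that its profile is flat. With the plan's power of 0.706 per test, the chance that exactly one test is significant is 2 × 0.706 × 0.294 = 0.415 if the tests are independent, and less if they are positively correlated. Reading a profile off which tests reach significance would then often suggest a pattern that does not exist. A direct comparison between tests needs a common scale, and none is specified.

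**The case against.** The strongest reply is that adjustment is already in the plan. The quoted sentence includes a covariate version, age and education are collected and named as adjustment variables, and scaled scores remain possible. A condensed article may leave the covariate list to a fuller document. All of this stands: the confounding attaches to the unadjusted version only, and the missing covariate list is not itself the point. What remains is a stated choice. Both versions are to be used to determine group differences, on raw scores, with neither put first. Scaled scores are only an option, and the Introduction says that Mindmore Remote norms are still being collected.

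Three stronger readings are tempting, and the documents do not support them:

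- **That the group contrasts would mostly measure age.** The article expects groups to differ in age variance. It states no group means and no age slopes, so the bias may be small.
- **That profile shape will not be tested at all.** Only the descriptive data are said to be presented test by test; the form of the ANOVA is open. The supportable statement is that no such analysis is described.
- **That controls should be recruited to age quotas.** One group of 50 controls serves six diagnoses, about eight per diagnosis (50/6). Matching to the pooled patient ages would not secure overlap with each group, and a broad age spread is a reasonable basis for covariate adjustment.

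It can also be said that the objective offers performance across tests only as an example of a profile, and that the Sample size section treats a different profile as a difference in level. That is a possible reading. But a difference in level on separate tests does not show how performance is distributed across them, which is the one example the objective gives.

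**Conclusion.** The point holds in limited form. The plan gives unadjusted raw-score group tests the same inferential standing as adjusted ones, and it describes no analysis of the pattern across tests on a common metric, although research question 2 concerns profiles. No stated figure is wrong.

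The size of the age bias cannot be established from the document. About 32% false rejections is what an age-score correlation of 0.3 and an age gap of 1 SD would produce at 50 v 50. Both inputs are assumptions, and the range in the table shows how strongly the result depends on them.

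The primary outcome, the within-participant association between paired tests, does not depend on these group comparisons. The issue is worth correcting because the planned data allow a better analysis.

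**What to change.** In the Data analysis plan, before any group comparison is examined:

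1. Name the comparison adjusted for age, education and gender as the inferential one. Report unadjusted means descriptively, without tests.
2. Put all tests on a common metric with the same direction, for example z-scores referenced to controls and adjusted for age and education separately for each test, with the sign of completion times reversed.
3. Fit one mixed model with a participant random effect, and use the group-by-test interaction as the test of profile difference. Optionally add method (Mindmore v traditional) as a further factor, to see whether both batteries give the same profile.

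The cost is modest extra analysis, with no new data and no change to recruitment. Two statistical downsides should be stated: control-referenced scores carry estimation error from only 50 controls, and adjusted comparisons lose precision where group ages overlap little.
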